## Abstract

Previous research has proposed a range of support interventions to mitigate the adverse impact of caregiving on the daily life of caregivers of relatives with dementia. However, the effectiveness of these interventions shows a high variability. Informal caregivers usually lack the time and/or live too far from conventional facilities to do physical exercise, especially those who live in rural areas. Thus, home-based interventions may be more efficacious due to their greater convenience for this population. The present work proposes and describes a study protocol for a randomized control trial that will analyze the efficacy and cost-effectiveness of a home-based, structured individual physical exercise intervention to improve the health-related quality of life and the mental health of female informal caregivers of relatives with dementia. The nine-month-long intervention will comprise participation in two supervised physical exercise sessions per week at the caregiver’s home. The proposed study outcomes will be: (1) feasibility of and adherence to the home-based provision of the intervention; (2) improvement in physical fitness and quality of life; and (3) reduction in subjective burden, psychological symptomatology and depression. Analyses will also be performed to determine the cost-effectiveness after the intervention. In conclusion, this intervention might thus represent a tailored and feasible strategy to help caregivers cope with the physical and psychological stress resulting from caregiving-related responsibilities, and it could represent a novel cost-effective support home-based intervention for caregivers.

## 1. Introduction

Previous research has shown that about 46.8 million individuals had dementia worldwide in 2015, and that this amount will peak at 74.7 million and 131.5 million in 2030 and 2050, respectively [1]. Therefore, and in accordance with this trend, it is expecting that the number of required caregivers to assist patients with dementia in the world will also significantly increase [2].

Spain has one of the highest rates of dementia worldwide. Moreover, the prevalence of the disease in this country significantly varies with the age of the population: between 5.4% and 14.9% in subjects who are aged 65 years or older and between 7% and 19.2% in 70-year-old subjects or older [3]. 

Most individuals with dementia are cared for at home by an unpaid informal caregiver [4,5]. In the majority of cases, the informal caregiver is a female family member, typically the spouse or daughter, who is aged between 45 and 65 years, who resides at the home of the care-recipient [2,6,7,8].

Although the role of caregiver may be perceived as satisfying and rewarding [9], the progressive and protracted deterioration of the state of health of individuals with dementia [8,10] requires caregivers to provide them with continuous support in all areas of life for long periods of time [11]. Moreover, the exact length of these long periods, as well as all the things that may happen to the subject with dementia, is usually unknown by informal caregivers. As a consequence, the exercise of the role of the caregiver leads to a wide variety of physical, psychological, social and financial difficulties [7,12,13,14,15]. In this regard, the adverse effects on physical health and quality of life are diverse [16,17,18,19,20]. Informal caregivers show higher rates of hypertension and other cardiovascular-related disorders [21,22], as well as lower aerobic endurance [23] than non-caregivers. Informal caregivers have reported having severe back pain due to alterations in the trunk muscle extensor strength [8,20], and other osteomuscular disorders [4]. At the psychological level, it has been found that informal caregivers experience high levels of subjective burden, distress, and a wide variety of psychological disorders [5,13,21,24,25,26,27,28,29], as well as sleep problems [30,31,32]. In addition, as part of their role, caregivers also suffer other symptoms such as hostility, aggression, somatization, irritability, hallucinations, delusions, restlessness, and disinhibition [2,33,34,35]. Regarding social and financial troubles, informal caregivers usually expend the most of their time and economic resources in providing the patient with care; this leads to a reduction in leisure activities [5] and, probably, to social isolation. Accordingly, the quality of life of informal caregivers of patients with dementia is also seriously affected [26].

In the scientific literature, we have identified different kinds of interventions aimed to try to reduce the adverse impact of the caregiving-related duties on informal caregivers’ physical and psychological health as well as quality of life. While some of these interventions have been focused on improving the health-related quality of life of caregivers and care-recipients as well as on positively impacting the society, in general, and the care-recipient’s direct environment, in particular [36,37], a different series of interventions have been focused on reducing the experienced psychological distress and subjective burden in caregivers and care-recipients [11]. These interventions include support groups, respite care, training of person with dementia in developing caring tasks efficiently, and other multicomponent approaches [37,38,39,40]. In addition of these interventions, and according to the review by Ploeg et al., [9] there have also been a series of web-based interventions carried out, that have led to a reduction in a range of psychological symptoms in caregivers of patients with dementia [9]. According to some other literature reviews [11,41,42,43], some randomized controlled trials (RCT) have also been conducted for caregivers, even web-based interventions [9]. However, among these RCTs, relatively few RCTs were well-designed and, despite being clinically meaningful, they have only showed limited effects on various aspects of caregivers’ wellbeing, such as confidence, self-efficacy, depression or quality of life [44,45], or have reported inconsistent results for this population [46].

Previous research has also shown that exercise-based therapies are effective and feasible methods of improving health-related quality of life (physical and psychological) in patients [47] and caregivers [48,49,50,51,52,53]. These interventions have usually resulted in an increase of participants’ physical activity level [21,23,52]; have positive effects on their physical fitness [48]; and alleviate fatigue and subjective burden [43,50,52,54]. Other studies have found that exercise-based programs improve caregivers’ psychological health. The intervention programs of these studies included endurance exercise [51]; walking [54,55]; or yoga [56,57]. However, the results of these studies have to be considered cautiously, because only a few studies have designed the experiment on the basis of a RCT approach [23], and the available RCT-based studies used small sample sizes [58]. In addition to this limitation, the heterogeneity of the examined variables, such as duration of the intervention, physical exercise intensity, weekly dose of activity, as well as a broad range of used exercises, also make it difficult to generalize the results to a larger population [43,59,60]. 

On the other hand, a noteworthy fact is that informal caregivers usually have limited time to be engaged in preventive health-related activities, such as physical exercise [61]. Indeed, caregivers of relatives with dementia find it dificult to leave their home or demanding flexibility, due to their caregiving-related responsibilities. Moreover, the long distances to regular services of provision with the opportunity to do physical exercise or to conventional facilities, such as a gym, for example, when the caregiver lives in small and/or rural municipalities, do not help either caregivers get involved in physical exercises programs [62]. Thus, the home environment might be considered an advantageous context for the provision of an intervention that is based on physical exercise, since it means less time and even less financial resources for participants than the conventional community-based programs [23]. In addition, home-based interventions may also improve participants’ adherence to the intervention [63,64]. In this regard, previous research has shown that a home-based support program for non-professional caregiver generates more positive effects than its counterpart [65]. The main reasons are that the first kind of intervention offers to participants individual tailoring; they are less economically demanding and may be more easily accessed for many caregivers [9], especially for those who live in remote areas, such as rural regions [66].

To the best of our knowledge, there is a lack of studies assessing the cost-utility of exercise-based programs provide in home-based contexts for caregivers of relatives [67]. Moreover, there are no programs—within the public sanitary or welfare system—that provide informal caregivers with individual face-to-face programs at caregivers’ homes in Spain. In addition, there is a lack of RCTS-based interventions evaluating the cost-effectiveness of a home-based physical exercise program for informal caregivers. Therefore, RCTs of interventions that particularly target the needs of individual caregivers, and that evaluate the cost-effectiveness and impact of home-based physical exercise interventions on informal caregivers’ physical and psychological status—quality of life—are warranted [42]. Results of these interventions might contribute by being the basis for future health care policies that establish home-based health promotion services and facilitate financial support for these initiatives. In accordance with research gaps and expectations, the aim of the present study is to describe a protocol for the evaluation of the cost-effectiveness and the effects of an adapted home-based exercise program for female family caregivers on their health-related quality of life. Thus, several dimensions of health will be evaluated: health-related fitness variables (strength, endurance, flexibility, balance, and motor function); subjective burden and depression, psychological symptomatology and global health-related quality of life.

## 2. Material and Methods

### 2.1. Design

A 9-month-long RCT will be performed to elucidate the cost-utility of a physical exercise program under the supervision of the main researcher of the current proposal, who is MSC in Health Economics and Pharma-economy. Participants will be randomly assigned to either the tailored home-based exercise group (intervention group) or the non-exercise group (control group). Assessment will be performed at baseline (pre-intervention assessment), 3 months, and 9 months after the intervention (post-intervention assessments) and 12 months after the intervention (post-intervention follow-up assessment); see Figure 1. The study is registered under clinical trial identifier ISCRCTN80414567, and will be conducted in accordance with the updates of the Declaration of Helsinki.

### 2.2. Participants

Participants will be recruited in cooperation with regional supporting associations for relatives of individuals with dementia. Potential participants will be identified and screened for eligibility in accordance with the study inclusion and exclusion criteria by trained members of the research team. The inclusion criteria will be: being a female caregiver of a relative with dementia; living at home with the patient with dementia; providing the relative with dementia with at least 20 hours of unpaid in-person care per week; being age 50 years or older; having no medical condition that could limit participation in a moderate-intensity exercise program; not having participated in any regular physical activity program, that is, having been engaged in less than two 20-minutes-long sessions of exercise per week during the 36 months prior to the intervention; not having changed medication or doses of medication for at least 3 months prior to study; and not having plans to move from the place of residence within the 12-month-long study. The exclusion criteria will be: having any external economic or personal support for caregiving of the patient with dementia. A written copy of the study protocol will be sent to all potential participants. In addition, at the first session of assessment, participants’ potential doubts will be solved by the member of research team. A signed informed consent will be requested to participate from all eligible participants prior to inclusion in the study.

#### 2.2.1. Sample Size Calculation

The required sample size will be estimated using the utility score of the Spanish version of the EQ-5D-3L questionnaire as primary outcome, and taken into account that this is an experimental study that will compare two groups with a significance level alpha = 0.05 and 80% of the statistical power that is required to detect a minimal clinically significant difference of 0.20 and SD = 0.12 [68].

On the other hand, we have also to consider the costs of the intervention added to the conventional care provided by the public health system, which will be 1680 € per caregiver. This amount will include the personal trainer’s salary, insurance, and 2 h/week travel-related costs.

A third aspect refers to the cost-efficiency ratio expressed as cost per quality-adjusted-life-years (QALYs). This will range between 10,000 and 50,000 € per QALYs [69], and we will use a conservative estimated sum = 30,000 € per QALYs. A cost-efficiency ratio = 0.21 corresponds to a 0.06 QALYs. In view of the above, a sample size of n = 50 caregivers distributed in two groups—control group and intervention group—is required to achieve a statistical power of 80% with a 95% of confidence interval, using an analysis of variance in parallel to parametric testing and anticipating a potential drop-out rate of 20%. In addition, in order to improve the confidence interval, a bootstrapping technique will also be used.

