We are also interested in evaluating the cost-effectiveness of the physical exercise program on the whole health of caregivers. In this sense, the most widely used methodological approach is to measure the consequences in terms of quality-adjusted life years (QALYs) that will be gained by the caregivers after the intervention, because it can combine gains in quantity of life and gains in quality of life in a single metric [94]. For this reason, we have selected the EQ-5D-3L, a well-known tool for evaluating the cost utility of the targeted intervention. Additionally, as we have previously described, several standardized measures will be also used to assess fitness, health-related outcomes, and psychological symptoms among participants. These variables have been selected because, according to the available scientific literature, several previous research studies have frequently documented that informal caregivers usually report lower scores than other populations in fitness, health-related quality of life and psychological wellbeing [20,24,29,92]. This will generate feasible data concerning the effectiveness of the intervention for caregivers. In this regard, and according to previous research [58], it is expected that there will be an improvement on health-related quality of life, and an increase in fitness level, as well as a decrease of burden and psychological symptoms in the caregivers subjected to the present intervention. In fact, potential indirect positive effects could be reported for the care recipients [58], due to the improvements of their caregivers.

If the present study protocol contributes to confirming the effectiveness of the intervention for informal caregivers of relatives with dementia, this study protocol and the research study proposed here might be applied to other caregiver populations such as family caregivers of relatives with Parkinson’s Disease, stroke, cancer or even to caregivers who do not reside with the care-recipient, such as neighbors or friends.

Finally, we have to point out the main limitation of the present study. We are referring to the relatively small sample size, which may limit the generalization of the results to other contexts. However, the sample size is adequate for assessing the effectiveness of the targeted intervention, and future research efforts will have to determine the required adjustments for future studies, larger cohorts or other populations.

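### The sample size of 50 for 80% power does not follow from the printed utility difference of 0.20 with SD 0.12, and the section leaves unclear whether that difference or a 0.06 QALY gain drives it

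*Protocol article*

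**What the plan says.** Section 2.2.1 (Sample Size Calculation) takes the EQ-5D-3L utility score as the primary outcome. It will "compare two groups with a significance level alpha = 0.05" and 80% power, to "detect a minimal clinically significant difference of 0.20 and SD = 0.12".

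The section then adds two economic elements: the programme cost, "which will be 1680 € per caregiver", and a threshold of 30,000 € per QALY. From these it states: "A cost-efficiency ratio = 0.21 corresponds to a 0.06 QALYs". No SD is given for the QALY figure.

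Referring back to all of this together, it concludes that "a sample size of n = 50 caregivers distributed in two groups" is "required to achieve a statistical power of 80% with a 95% of confidence interval", by analysis of variance and with 20% drop-out anticipated.

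Section 4 (Discussion) names the small sample as the main limitation as regards generalisation, then says: "However, the sample size is adequate for assessing the effectiveness of the targeted intervention".

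**The concern.** A difference of 0.20 against an SD of 0.12 is 1.67 standard deviations. An effect that large needs very few participants, so a requirement of 50 looks out of line with it. Either one of the printed figures is wrong, or 50 came from something else. The only other candidate in the section is 0.06 QALYs, and the text does not say whether that figure entered the calculation.

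At stake is what the trial may claim to be able to detect. A reader cannot tell whether the 80% refers to a large utility difference, to the break-even QALY gain, or to some intermediate value that is not printed. The Discussion then relies on the result when it calls the sample adequate.

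**Working it through.** **Inputs from section 2.2.1:** alpha 0.05; power 80%; utility difference 0.20; SD 0.12; drop-out 20%; total 50; cost 1680 €; threshold 30,000 € per QALY; gain 0.06 QALYs.

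**Assumptions:** two-sided test and 1:1 allocation (neither is stated), and a two-sample t-test with power from the noncentral t distribution. Completers: 50 × 0.8 = 40, or 20 per arm.

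**1. Attempt to reproduce 50 from the declared target.**
- d = 0.20 / 0.12 = 1.667.
- n per arm for 80% power = 6.76, rounded up to 7, so 14 completers. Enrolled: 14 / 0.8 = 17.5, so 18.
- The normal approximation, 2(1.960 + 0.842)² / d² = 15.70 / 2.778 = 5.65, gives 6 per arm: 12 completers, 15 enrolled.
- One-sided: 10 (normal) or 12 (t) completers.
- Power with 20 per arm: 0.999.

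The figure of 50 is not reproduced. Reading the pair as swapped (difference 0.12, SD 0.20) gives 90 completers, 113 enrolled.

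**2. What would give 50.** With 20 per arm, 80% power is reached at d = 0.909.
- At SD 0.12 the difference would have to be 0.909 × 0.12 = 0.109.
- At a difference of 0.20 the SD would have to be 0.20 / 0.909 = 0.220.

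Neither value is printed.

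**3. What 0.06 is.** 1680 / 30,000 = 0.056, which rounds to 0.06. It is the QALY gain at which the programme cost meets the threshold.

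**4. If 0.06 were the target (illustration only).** The section gives no SD for QALYs, so one has to be assumed.

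| Assumed SD | d | Per arm | Completers | Power, 20 per arm | Power, 25 per arm |
|---|---|---|---|---|---|
| 0.12 (the utility SD, borrowed) | 0.500 | 64 | 128 | 34% | 41% |
| 0.09 (0.75 year × 0.12) | 0.667 | 37 | 74 | 54% | 64% |

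- One-sided, SD 0.12, 20 per arm: 46%.
- The one-sided normal formula for 0.06 with SD 0.12 gives 50 per arm. That is 100 completers before drop-out, whereas the text has 50 in total with drop-out already counted.
- Baseline adjustment multiplies the SD by √(1 − r²). For 80% power with 20 per arm the adjusted SD must be 0.06 / 0.909 = 0.066. This needs r of about 0.84 at SD 0.12 (√(1 − (0.066/0.12)²)) or about 0.68 at SD 0.09.
- A change-score analysis at SD 0.12 needs 40 completers, and so 50 enrolled, if r is about 0.85. No correlation is printed.

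**5. If end-point utility is tested instead of QALYs.** Power then depends on how the 0.06 accrues (equal baselines, SD 0.12, 20 per arm):
- constant gap over 9 months: 0.06 / 0.75 = 0.08; power 54%;
- gap growing linearly from zero over 9 months: 2 × 0.06 / 0.75 = 0.16 at month 9; power 98%;
- the same over 12 months: 2 × 0.06 / 1 = 0.12 at month 12; power 87%.

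**The case against.** The strongest reply is that the only difference the section says it aims to detect is 0.20, and for that the trial has more power than claimed. The 0.06 is introduced as a further, economic consideration. It is a break-even value in QALYs, and SD 0.12 is attached to a utility difference. Pairing the two mixes scales, and the unadjusted 34% also ignores the regression adjustment for baseline EQ-5D planned in section 3.1.1. All of this stands.

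A reader might therefore be tempted to infer that the trial is underpowered for its own target, needs 128 completers and would miss the relevant gain about two times in three. The document does not support that. It never states that the study is powered for 0.06, it gives no SD or correlation for QALYs, and the power figure moves widely with scale, trajectory and adjustment.

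Nor does it support the inference that a non-significant result would be reported as no effect. The Cost Utility Analysis part of section 2.5 plans a bootstrap 95% interval, an acceptability curve and scenarios that run across that interval.

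The reply does not rescue the printed sample size. Being overpowered for 0.20 does not make 50 the number required for 80% power. A misprint in 0.20 or 0.12 is quite possible. The source is not at hand, and a misprint would confirm that the section needs correcting.

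**Conclusion.** The point holds for the declared target. The printed difference, SD, alpha and power require 14 completers (18 enrolled), not 40 completers from 50, and 40 completers would have over 99% power for 0.20. This rests only on a standard two-group comparison with equal arms. One-sided testing, the normal approximation or swapping the two numbers does not recover 50.

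It also holds that the section does not say which quantity drives 50, because its conclusion draws on both 0.20 and the break-even 0.06 QALYs. The figures for 0.06 are illustrations under assumed SDs: about 34% to 54% unadjusted, and higher with baseline adjustment or if end-point utility is tested. They show that 80% power for 0.06 cannot be claimed from what is printed. They do not establish the design's actual power for it.

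**What to change.** Keep 50 participants and correct the text:

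1. Check 0.20 and 0.12 against the cited source and correct whichever is misprinted.
2. Name one target difference with its SD on one scale, utility or QALY. State the sidedness, the allocation ratio and any baseline correlation used.
3. State what 40 completers deliver: with SD 0.12 and a two-sided unadjusted test, 80% power for a difference of about 0.11. Recompute this if the SD changes.
4. Label 0.06 as the break-even gain (1680 / 30,000 = 0.056, rounded). Do not claim 80% power for it unless a stated QALY SD and correlation support that.
5. In the Discussion, replace the adequacy sentence with the detectable difference.

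The cost is a reworded sample size section and one Discussion sentence. No participants are added and the design does not change. If the source confirms 0.20 and 0.12, the text would have to say that 50 exceeds what they require and give another reason for choosing it.

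### The printed inputs do not give n = 50 at 80% power: a utility difference of 0.20 with SD 0.12 needs about 18 randomised, and no power is shown for the 0.06 QALY gain

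*Protocol article*

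**What the plan says.** Section 2.2.1 names the EQ-5D-3L utility score as the primary outcome for sizing. It sets "a significance level alpha = 0.05 and 80% of the statistical power", and the target is "to detect a minimal clinically significant difference of 0.20 and SD = 0.12".

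The section then brings in the programme cost of 1680 € per caregiver and a threshold of 30,000 € per QALY, and states: "A cost-efficiency ratio = 0.21 corresponds to a 0.06 QALYs". From all of this together it concludes that "a sample size of n = 50 caregivers distributed in two groups" "is required to achieve a statistical power of 80"%, allowing for 20% drop-out. It adds that bootstrapping will be used to improve the confidence interval.

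Section 3.1.1 says that the main purpose is cost-effectiveness and that the primary outcome is EQ-5D-3L utility expressed in QALYs, adjusted for baseline EQ-5D by regression. The Discussion (section 4) calls the small sample the main limitation, yet says that "the sample size is adequate for assessing the effectiveness of the targeted intervention".

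**The concern.** The section prints its inputs and its result, so a reader should be able to get from one to the other. A difference of 0.20 against an SD of 0.12 is a standardised effect of 1.67, which is very large. A trial sized for it at 80% power would be far smaller than 50. The second figure, 0.06 QALY, is in another unit and has no SD, so no sample size can be computed from it. The text does not say which of the two fixes n.

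The stated 80% power is what a reader will use to interpret the primary result. If it belongs to no identified target, nobody can say what a non-significant or imprecise result rules out. This matters most for the cost-utility question, because the funding decision at 30,000 € per QALY turns on a gain near 0.06 QALY and the plan shows no power or precision there.

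**Working it through.** **Inputs from the article.** Alpha 0.05, power 80%, difference 0.20, SD 0.12, total 50, drop-out 20%, cost 1680 €, threshold 30,000 € per QALY (all section 2.2.1).

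**Assumptions.** Two-sided testing, because the section speaks of "a statistical power of 80% with a 95% of confidence interval", and 1:1 allocation. Fifty randomised with 20% drop-out leaves 50 × 0.80 = 40 evaluable, or 20 per arm.

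**1. Trying to reproduce 50 from the stated utility target.**
- Standardised effect: d = 0.20 / 0.12 = 1.667.
- Normal approximation: n per arm = 2 × (1.960 + 0.842)² / d² = 15.70 / 2.778 = 5.65, so 6 per arm, 12 evaluable and 12 / 0.80 = 15 randomised.
- Exact t-test: 6.76, so 7 per arm, 14 evaluable and 14 / 0.80 = 17.5, so 18 randomised.
- One-sided testing lowers this to 13 to 15 randomised.
- Power at 20 evaluable per arm: 99.9%, not 80%.

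**2. What 20 evaluable per arm would need for 80% power.** The detectable d is 0.909. This corresponds to:
- a difference of 0.909 × 0.12 = 0.109 at SD 0.12; or
- an SD of 0.20 / 0.909 = 0.22 for a difference of 0.20; or
- an SD of 0.06 / 0.909 = 0.066 for a difference of 0.06.

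None of these is in the article.

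**3. Expected precision.** The 95% CI half-width for a utility difference is 2.024 × 0.12 × √(2/20) = 0.077.

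**4. The cost figures.**
- 1680 / 30,000 = 0.056, which rounds to 0.06. This is the gain at which the programme cost alone equals the threshold.
- The section introduces its ratio as cost per QALY, but 0.21 carries no unit.
- Dividing 1680 by the other ends of the quoted threshold range gives 0.168 (10,000) and 0.034 (50,000). None of the three quotients is 0.21.

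**5. Illustration only: 0.06 QALY under assumed QALY SDs.** The article gives no QALY SD. Power at 20 per arm, two-sided t-test:

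| Assumed QALY SD | Baseline adjustment | Power for 0.06 QALY |
|---|---|---|
| 0.15 | none | 23% |
| 0.12 (borrowed from utility) | none | 34% |
| 0.08 | none | 64% |
| 0.12 | r = 0.5 (residual SD 0.104) | 43% |
| 0.12 | r = 0.7 (residual SD 0.086) | 58% |
| 0.12 | r = 0.8 (residual SD 0.072) | 73% |

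Residual SD is SD × √(1 − r²), and each r is an assumption. Power reaches 80% only at a residual SD of about 0.066 or less.

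**6. Nearest match.** A difference of 0.06 with SD 0.12, one-sided by normal approximation, gives 2 × (1.645 + 0.842)² / 0.25 = 49.5, so 50 *per arm*. That is 100 evaluable and 125 randomised, whereas the article has 50 across two groups with drop-out already allowed for.

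**The case against.** A reader might infer more than this: that the trial has only about 34% power for its real question. The article does not support that as a finding.
- The 34% applies a utility SD to a QALY difference and leaves out the baseline adjustment planned in section 3.1.1.
- It also treats 0.06 QALY as if it were 0.06 of utility. QALYs are utility multiplied by time, so the two are equal only for a difference that is constant over a full year. A linear rise to 0.20 at nine months gives ½ × 0.20 × 0.75 = 0.075 QALY, so 0.20 of utility and 0.06 QALY are not necessarily in conflict.
- The text ties detection only to 0.20, for which 50 is generous. It presents 0.06 as a break-even figure and does not expressly claim 80% power for it.

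A second tempting inference is that net benefit is exactly zero at 0.056 QALY, so the trial could never show cost-effectiveness. That requires the incremental cost to be exactly 1680 €. Sections 2.4.2 and 3.1.1 also count health-service use, and fewer visits would move the break-even point.

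It is also fair to say that the cost utility part of section 2.5 already plans estimation, with a bootstrap interval, an acceptability curve and sensitivity analyses, and gives bootstrapping its proper purpose there. The Discussion does admit that the sample is small.

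These objections remove the low-power claim. They do not explain where 50 comes from, what the 80% refers to, or how 0.21 was obtained.

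**Conclusion.** The sample-size statement is wrong as written. The one fully specified target, 0.20 with SD 0.12, needs about 18 randomised rather than 50, and at 50 randomised its power is about 99.9% rather than 80%. For that target the trial is oversized, not underpowered. The 0.21 cannot be traced. The 0.06 QALY has no SD, so adequate power for it is neither shown nor refuted. Under the assumptions tabulated, power for 0.06 QALY runs from 23% to 73%, and that range illustrates only how much depends on the missing SD.

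The conclusion on 0.20 rests on two-sided testing, 1:1 allocation and 20 evaluable per arm. One-sided testing or the normal approximation changes the required number by a few caregivers and does not bring it near 50.

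**What to change.** Keep n = 50 and rewrite the statement around what it delivers:

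- *Utility.* With 50 randomised and 20% drop-out (20 evaluable per arm), SD 0.12 and two-sided alpha 0.05, power is above 99% for a utility difference of 0.20. The smallest utility difference detectable with 80% power is about 0.11, and the expected 95% CI half-width is about 0.077. The 0.11 describes what the sample can detect; it does not replace the minimal clinically significant difference.
- *QALYs.* State separately, in QALY units, the precision or power for 0.06 QALY, with an explicit QALY SD, its source and a range. Say that the trial is not shown to have 80% power for that gain.
- *The 0.21.* Derive it or delete it.
- *Bootstrapping.* Reword the sentence in section 2.2.1 to agree with the cost utility part of section 2.5: it reports sampling uncertainty and adds no precision.
- *Discussion.* Limit the adequacy sentence to the utility difference that the sample size supports.

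The cost is protocol wording and the choice of a QALY SD. No extra caregivers are needed. The sponsor gives up an 80% power claim that has no identifiable target.
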